**NOTE:**

For participants with Grade 3 or 4 immune-related endocrinopathy where withhold of sintilimab is required, sintilimab may be resumed when AE resolves to ≤ Grade 2 and is controlled with hormonal replacement therapy or achieved metabolic control (in case of T1DM).

### **Infusion related reactions**

Severe infusion-related reactions, including hypersensitivity and anaphylaxis, have been reported in patients receiving sintilimab. For severe infusion reactions, infusion should be stopped and sintilimab permanently discontinued (see Table 2). Patients with mild or moderate infusion reaction may continue to receive sintilimab with close monitoring; premedication with antipyretic and antihistamine may be considered.

**Table 2 Sintilimab Infusion Reaction Dose modification and Treatment Guidelines**

| NCI CTCAE Grade                                                                                                                                                                                                                                                                                                                                                                     | Treatment                                                                                                                                                                                                                                                                                                                                                                                                                                                                                                                                                                                                                                                                                                                                                                              | Premedication at Subsequent Dosing                                                                                                                                                                                         |
|-------------------------------------------------------------------------------------------------------------------------------------------------------------------------------------------------------------------------------------------------------------------------------------------------------------------------------------------------------------------------------------|----------------------------------------------------------------------------------------------------------------------------------------------------------------------------------------------------------------------------------------------------------------------------------------------------------------------------------------------------------------------------------------------------------------------------------------------------------------------------------------------------------------------------------------------------------------------------------------------------------------------------------------------------------------------------------------------------------------------------------------------------------------------------------------|----------------------------------------------------------------------------------------------------------------------------------------------------------------------------------------------------------------------------|
| Grade 1
Mild reaction; infusion interruption not indicated; intervention not indicated                                                                                                                                                                                                                                                                                    | Increase monitoring of vital signs as medically indicated until the participant is deemed medically stable in the opinion of the investigator.                                                                                                                                                                                                                                                                                                                                                                                                                                                                                                                                                                                                                                         | None                                                                                                                                                                                                                       |
| Grade 2
Requires therapy or infusion interruption but responds promptly to symptomatic treatment (e.g., antihistamines, NSAIDs, narcotics, IV fluids); prophylactic medications indicated for ≤24 hrs                                                                                                                                                                     | Stop Infusion.
Additional appropriate medical therapy may include but is not limited to:
IV fluids
Antihistamines
NSAIDs
Acetaminophen
Narcotics
Increase monitoring of vital signs as medically indicated until the participant is deemed medically stable in the opinion of the investigator.
If symptoms resolve within 1 hour of stopping drug infusion, the infusion may be restarted at 50% of the original infusion rate (e.g. from 100 mL/hr to 50 mL/hr). Otherwise dosing will be held until symptoms resolve and the participant should be premedicated for the next scheduled dose.
Participants who develop Grade 2 toxicity despite adequate premedication should be permanently discontinued from further study drug treatment | Participant may be premedicated 1.5h (± 30 minutes) prior to infusion of _____ with:
Diphenhydramine 50 mg po (or equivalent dose of antihistamine).
Acetaminophen 500-1000 mg po (or equivalent dose of analgesic). |
| Grades 3 or 4
Grade 3:
Prolonged (i.e., not rapidly responsive to symptomatic medication and/or brief interruption of infusion); recurrence of symptoms following initial improvement; hospitalization indicated for other clinical sequelae (e.g., renal impairment, pulmonary infiltrates)
Grade 4:
Life-threatening; pressor or ventilatory support indicated | Stop Infusion.
Additional appropriate medical therapy may include but is not limited to:
Epinephrine**
IV fluids
Antihistamines
NSAIDs
Acetaminophen
Narcotics
Oxygen
Pressors
Corticosteroids
Increase monitoring of vital signs as medically indicated until the participant is deemed medically stable in the opinion of the investigator.
Hospitalization may be indicated.
**In cases of anaphylaxis, epinephrine should be used immediately.
Participant is permanently discontinued from further study drug treatment.                                                                                                                                                                                                  | No subsequent dosing                                                                                                                                                                                                       |
| Appropriate resuscitation equipment should be available at the bedside and a physician readily available during the period of drug administration.
For further information, please refer to the Common Terminology Criteria for Adverse Events v4.0 (CTCAE) at http://ctep.cancer.gov                                                       |                                                                                                                                                                                                                                                                                                                                                                                                                                                                                                                                                                                                                                                                                                                                                                                        |                                                                                                                                                                                                                            |

## **7.6 Concomitant therapy**

Since sintilimab is cleared from the circulation through catabolism, no metabolic drug-drug interactions are expected. The use of systemic corticosteroids or immunosuppressants before starting sintilimab should be avoided because of their potential interference with the pharmacodynamic activity and efficacy of sintilimab. However, systemic corticosteroids or other immunosuppressants can be used after starting sintilimab to treat immune-related adverse reactions.

### **Permitted medications**

Oral contraceptives, hormone replacement therapies, or other maintenance therapy are allowed to continue

Use of inhaled corticosteroids and mineralocorticoids is allowed

Megestrol administered as an appetite stimulant is acceptable

Prophylaxis of nausea and vomiting is allowed as per institutional practice

Use of antimicrobial and/or anti viral prophylaxis according to institutional guidelines is allowed. This also include the use of medications to prevent hepatitis B reactivation.

Flu vaccination should be given during flu season but live attenuated vaccines must be avoided.

### **Prohibited medications**

Patients should not receive long term treatment with corticosteroids other than intermittent corticosteroids for prophylaxis or for treatment of autoimmune conditions. Non steroidal hormones for non-lymphoma related conditions are permitted

Any other chemotherapy agent is not allowed.

Traditional herb medicine should not be administered.

Patients are not allowed to receive immunostimulatory medications, including but not limited to IFN $\alpha$ , IFN gamma or IL2.

Patients are not allowed to receive immunosuppressive medications, including but not limited to cyclophosphamide, azathioprine, methotrexate, lenalidomide and thalidomide.

## 8 STUDY ASSESSMENTS

### 8.1 Schedule of Events

**Table 3 Schedule of Events and related footnotes summarize information on the timing of study assessments.**

| Protocol Activities                                            | Pre-Treatment Assessment | Induction Phase              |                           | Maintenance Phase              |                                               | Follow-up Phase                |                     |
|----------------------------------------------------------------|--------------------------|------------------------------|---------------------------|--------------------------------|-----------------------------------------------|--------------------------------|---------------------|
|                                                                |                          | D1 (from Cycle 1 to Cycle 6) | EOI (14-21d from cycle 6) | D1 (from Cycle 7 to 34 cycles) | Evaluation (14-21d from cycle 12, 18, 24, 30) | EOT (within 30d from cycle 34) | FUP (every 4 month) |
| Informed Consent                                               | X                        |                              |                           |                                |                                               |                                |                     |
| Medical history                                                | X                        |                              |                           |                                |                                               |                                |                     |
| Bone marrow aspiration biopsies                                | X                        |                              |                           |                                |                                               |                                |                     |
| Tumor biopsies                                                 | X                        |                              |                           |                                |                                               |                                |                     |
| Pregnancy test (women of childbearing age)                     | X                        |                              |                           |                                |                                               |                                |                     |
| Physical examination                                           | X                        | X                            | X                         | X                              | X                                             | X                              |                     |
| ECOG                                                           | X                        | X                            | X                         | X                              | X                                             | X                              |                     |
| CBC, urine, and stool analysis                                 | X                        | X                            | X (CBC)                   | X                              | X (CBC)                                       | X (CBC)                        |                     |
| DIC                                                            | X                        | X                            |                           | X                              |                                               |                                |                     |
| Liver and renal function, electrolytes, LDH, B2M, CRP, Pro-BNP | X                        | X                            | X                         | X                              | X                                             | X                              |                     |
| EBV DNA                                                        | X                        | X                            | X                         | X                              | X                                             | X                              |                     |
| UCG, EKG                                                       | X                        | X                            |                           | X                              |                                               |                                |                     |
| FT3, FT4, TSH                                                  | X                        | X                            |                           | X                              |                                               |                                |                     |
| HBV, HCV and HIV serology                                      | X                        |                              |                           |                                |                                               |                                |                     |
| Tumor Imaging (evaluation)                                     | X                        |                              | X                         | X                              | X                                             | X                              |                     |
| EORTC QLQ-C30                                                  | X                        |                              | X                         | X                              | X                                             | X                              |                     |
| Concomitant Medications                                        | X                        | X                            | X                         | X                              |                                               | X                              |                     |
| AEs Assessment                                                 |                          | X                            | X                         | X                              |                                               | X                              |                     |
| Survival                                                       |                          |                              |                           |                                |                                               | X                              | X                   |
| Pegaspargase                                                   |                          | X                            |                           |                                |                                               |                                |                     |
| Sintilimab                                                     |                          | X                            |                           | X                              |                                               |                                |                     |

### 8.2 Assessment of Tumor response

Tumor response is classified according to 2014 Lugano criteria[21] and 2016 Refinement of the Lugano Classification lymphoma response criteria in the era of immunomodulatory therapy[22]. The objective efficacy is divided into complete

remission (CR), partial remission (PR), stable (SD), disease recurrence or disease progression.

Response will be assessed at the interim (C3) and the end (C6) of induction therapy and the every 6 cycles of sintilimab treatment until completion of maintenance phase (EOT visit).

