## 6. STUDY DESIGN AND STUDY POPULATION

### 6.1 General Study Design

This phase II, open-label, single arm trial will evaluate the efficacy and safety of anti-PD-1 antibody in combination with pegaspargase in treatment of newly diagnosed advanced stage NK/T-cell lymphoma.

All eligible patients will receive induction treatment for six cycles of Anti-PD-1 antibody sintilimab plus pegaspargase (21-day cycle) and sintilimab monotherapy maintenance treatment for about 2 years (21-day cycle).

The follow-up period will last up to 2 years from the date of last subject enrollment.

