#### Response assessment

Response will be evaluated according to 2014 Lugano criteria and 2016 Refinement of the Lugano Classification lymphoma response criteria in the era of immunomodulatory therapy using CT scan and PET-CT scan.

Patients will be evaluated for safety and tolerability of study treatment.

Anti-tumor activity assessment will be performed at cycle 3 and 6, every 4 months in the first year of follow-up, followed by every 6 months in the second year of follow-up (end of study).

For patients who experience PD or who discontinue the study due to an adverse event (AE) or a serious adverse event (SAE), the full assessment (EOT) should be obtained 30 days of the last dose of study treatment or before another anticancer therapy is initiated, whichever is shorter.

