### **7.2 Maintenance phase**

Sintilimab 200mg administered intravenously on Day 1 of each 21-day cycle for up to 28 cycles in maintenance treatment.

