### **7.5 Management and monitoring of AEs**

Dose modifications: there will be no dose modifications in this study. Patients with severe chemotherapy toxicity or patients who delay chemotherapy for more than 2 weeks due to adverse events are recommended to withdraw from the study.

Sintilimab treatment may be temporarily suspended in patients experiencing toxicity considered related to study treatment. If corticosteroids are initiated for treatment of the toxicity, the must be tapered over > 1 month to <10 mg/day or oral prednisone or equivalent before sintilimab can be resumed. If sintilimab is withheld for > 12 weeks treatment can be resumed prior approval by the principal investigator. In Table 1 is reported a guideline for the management of patients who experienced specific adverse events (see also Appendix 5).

AEs associated with sintilimab exposure may represent an immunologic etiology. These immune-related AEs (irAEs) may occur shortly after the first dose or several months after the last dose of sintilimab treatment and may affect more than one body system simultaneously. Therefore, early recognition and initiation of treatment is critical to reduce complications. Based on existing clinical study data, most irAEs were reversible and could be managed with interruptions of sintilimab, administration

of corticosteroids and/or other supportive care. For suspected irAEs, ensure adequate evaluation to confirm etiology or exclude other causes. Additional procedures or tests such as bronchoscopy, endoscopy, skin biopsy may be included as part of the evaluation. Based on the severity of irAEs, withhold or permanently discontinue sintilimab and administer corticosteroids. Dose modification and toxicity management guidelines for irAEs associated with sintilimab are provided in Table 1.

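### Maintenance scans are timed by sintilimab cycle in 8.2 and Table 3 but by calendar in 6.1; under the cycle rule a dose hold postpones the next scan, and 2-year PFS and duration of response can look slightly longer

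*Protocol*

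**What the plan says.** **Cycle-based rule.** After the cycle 3 and cycle 6 assessments, section 8.2 requires response assessment "every 6 cycles of sintilimab treatment until completion of maintenance phase". Table 3 (section 8.1) has a maintenance column headed "Evaluation (14-21d from cycle 12, 18, 24, 30", followed by an EOT visit within 30 days of cycle 34. It also marks tumour imaging in the maintenance Day 1 column, and marks none in the FUP column.

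**Calendar-based rule.** Section 6.1 (Response assessment) keeps the cycle 3 and 6 scans and then goes "every 4 months in the first year of follow-up, followed by every 6 months in the second year of follow-up (end of study". The same section says "The follow-up period will last up to 2 years from the date of last subject enrollment".

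**Dosing.** Maintenance sintilimab is given on "Day 1 of each 21-day cycle for up to 28 cycles in maintenance treatment" (section 7.2). Section 7.4 makes the start of each cycle conditional on blood counts and on resolution of immune-related events. Section 7.5 adds: "Sintilimab treatment may be temporarily suspended in patients experiencing toxicity considered related to study treatment". It also says: "If sintilimab is withheld for > 12 weeks treatment can be resumed prior approval by the principal investigator".

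**Endpoint.** Under section 9.2.1, PFS runs from enrolment to progression, relapse or death. Two-year PFS and duration of response are secondary outcomes (section 5.2).

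**The concern.** When scans are counted in cycles, the imaging clock can stop when dosing stops. Patients whose drug is held for toxicity are then scanned later than the others, and progression that arises in the meantime is dated at the postponed scan. The time in between counts as progression-free. A single-arm trial has no control group in which this could cancel.

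The 2-year landmark is exposed because 34 cycles take almost exactly two years, so the last scheduled scan has little room before it. The protocol calls this a preparatory study for a larger randomised trial, and its PFS estimate may be used in planning that trial.

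**Working it through.** The protocol gives no figure for PFS, so the check is calendar arithmetic followed by an illustration under stated assumptions.

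**1. Do the two schedules agree?** Six cycles are 6 × 21 = 126 days = 18 weeks, or 126 / 30.44 = 4.1 months. With no delay this nearly matches the 4-month interval in 6.1. For the rest there are two readings:
- Follow-up is the phase after maintenance, as the Table 3 column groups suggest. Section 6.1 then sets no calendar scans during maintenance, and cycle count governs alone.
- Follow-up runs from enrolment, as its stated end two years after the last enrolment allows. Section 6.1 then overlaps maintenance and conflicts with 8.2 and Table 3, both after any hold and in year 2 (6 months against 4.1).

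**2. Interval after a hold.** If the next dose is 12 weeks late, the scan interval becomes 126 + 84 = 210 days.

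**3. Room before two years.** Take enrolment as cycle 1 Day 1 (day 0) and two years as day 730.5. Cycle 34 Day 1 is 33 × 21 = day 693, and the latest EOT is 693 + 30 = day 723. The slack is 730.5 - 723 = 7.5 days for the latest scan and 730.5 - 693 = 37.5 days for the earliest, or about 1 to 5 weeks. After a 3-week delay the window is days 714 to 744, so the scan may fall on either side of two years.

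**4. Which scan is the last before two years?** Assume evaluation scans 21 days after the cycle's dose, EOT 30 days after cycle 34, exponential PFS with a true 2-year rate of 50%, and progression dated only at scheduled scans. If the last scan before the landmark is on day L, apparent 2-year PFS is 0.5^(L/730.5).

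| Delay | Cycle-30 scan | EOT scan | L | Apparent 2-year PFS |
|---|---|---|---|---|
| none | 630 | 723 | 723 | 50.4% |
| 14 d, before cycle 30 | 644 | 737 | 644 | 54.3% |
| 42 d, before cycle 30 | 672 | 765 | 672 | 52.9% |
| 84 d, before cycle 30 | 714 | 807 | 714 | 50.8% |
| over 7.5 d, after the cycle-30 scan | 630 | after 730.5 | 630 | 55.0% |

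The effect does not grow steadily with the length of the hold, because a long hold can bring the cycle-30 scan close to the landmark. With EOT 21 days after cycle 34, the no-delay scan is on day 714 and a 14-day delay moves it to day 728. The estimate then falls slightly, from 50.8% to 50.1%. In these cases the longest unscanned stretch before the landmark is 730.5 - 630 = 100.5 days. That is worth 3.5 to 5.4 points above the truth for true rates of 30 to 70%.

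**5. Simulation.** Assumptions: one hold of 14, 42 or 84 days, starting before a random cycle from 2 to 34, and a true 2-year PFS of 30 to 70%. The change in apparent 2-year PFS against the same schedule without holds, in percentage points, was:

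| Patients with a hold | EOT 30 d after cycle 34 | EOT 21 d after cycle 34 |
|---|---|---|
| 20% | +0.1 to +0.9 | -0.3 to +0.5 |
| 50% | +0.4 to +2.2 | -0.5 to +1.4 |
| 100% | +0.7 to +4.4 | -0.8 to +2.5 |

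A second simulation (30 to 50% of patients held, true 2-year PFS 40 to 70%) gave about +0.3 to +1.4 points.

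**6. Scale.** The standard error at n = 22 is √(0.6 × 0.4 / 22) = 0.104. One patient is 1/22 = 4.5 points. At 50%, the 95% half-width is 1.96 × √(0.25 / 22), about 21 points.

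**The case against.** The strongest case against is that section 6.1 does set calendar scans, that the effect is minor and rests on assumptions, and that the primary endpoint is untouched. All of this stands. However, 6.1 does not settle the matter: it either starts after maintenance or contradicts 8.2 and Table 3, and the FUP column of Table 3 has no imaging to catch up with.

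A reader might go further in several ways that the documents do not support:
- **That the protocol has no calendar rule, so every hold must delay a scan.** Section 6.1 has one. Where it applies, a hold moves nothing.
- **That the bias runs strictly one way.** Against the truth, late detection cannot shorten apparent PFS. Against a no-hold schedule, the 2-year figure can fall slightly.
- **That holds have no upper limit.** Section 7.5 allows resumption after 12 weeks, but the Appendix 5 footnote, which names another product, calls for permanent discontinuation under its own 12-week conditions. The two texts disagree.
- **That progression during a hold cannot be seen until dosing restarts.** An evaluation due 14 to 21 days after a cycle already given still falls due during a hold that begins after that dose. Patients who discontinue for an adverse event have an EOT assessment under 6.1. The imaging mark under maintenance Day 1 is tied to dosing, so it supplies no scan during a hold.
- **That a 3-week delay necessarily carries the last scan past two years.** That depends on where in the 30-day window it is done.
- **That all scans, including those in induction, should be fixed to the calendar.** The primary endpoint is defined at the end of cycle 6. A fixed week-18 scan could come before cycle 6 is complete in a patient whose induction slipped.

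**Conclusion.** The point holds as a minor but real defect. Scan timing after induction is stated in two ways that do not agree or that leave maintenance to cycle count alone, and under the cycle rule a hold can delay detection of progression. The generally upward effect on 2-year PFS is commonly about 1 point. The ends of the range, -0.8 and +4.4, arise only when every patient has a hold. Duration of response is exposed in the same way, but no size was calculated for it.

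These sizes rest on assumed hold frequency and length, exponential PFS, enrolment on the first dosing day, and detection at scheduled scans only. Deaths, and progression found clinically between scans, would reduce them. PFS has no stated hypothesis, and the complete response test after cycle 6 is not affected by maintenance holds.

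**What to change.** Leave the cycle 3 and end-of-cycle-6 scans as they are. In 6.1, 8.2 and Table 3, state one calendar schedule for response scans after induction, done whether or not sintilimab is on hold. For example, use every 18 weeks, the interval already implied, with a window, and place the last scheduled scan at 24 months from enrolment. Counted from enrolment, that gives weeks 36, 54, 72 and 90 and month 24: five scans, against the present five (after cycles 12, 18, 24 and 30, and EOT). Say in 6.1 what follow-up means, and make the imaging marks under maintenance Day 1 and FUP in Table 3 agree with the single schedule.

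The cost is a wording change and a visit window, with about the same number of scans. The downside is that scan dates will no longer match cycle numbers in patients with holds.

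Separately, the hold-duration text in 7.5 and the Appendix 5 footnote must be reconciled by the sponsor. This review takes no position on which is right.
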